### Outcomes

#### Primary outcome

The primary outcome, clinical efficacy of materials, will be measured by use of the Fédération Dentaire Internationale (FDI) World Dental Federation instrument for assessing dental restorations, described in 2007
[28] and updated in 2010
[38]. This instrument contains three dimensions (18 items): biological (six items), functional (seven items) and esthetic (five items). Each item is assessed by clinical examination on a 5-point Likert scale (1 corresponding to a perfect restoration and 5 corresponding to a restoration that needs to be replaced), and collected in the CRF. All items but one are assessed by the dentist; the remaining item is patient-reported satisfaction. The primary outcome is the worst score for all items (ranging from 1 to 5) at 2-year follow-up (the best material will be the one with the lowest score).

Operators and evaluators, who will assign scores, will be trained in the FDI criteria by means of the e-calib web-based  software (http://zep01793.dent.med.uni-muenchen.de/moodle/) and group training sessions. They will use the evaluation kit specifically designed for evaluating the FDI criteria (EX-KIT 150/250, Deppeler, Rolle, Switzerland).

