### Sample size

We estimated the required sample size for the primary outcome (score between 1 and 5, 5 corresponding to the worst score) for the 18 items for each patient. Since the resulting score is an ordinal variable, we used Zhao’s formula, which is based on the expected distribution of responses in each of the five possible ratings
[39]. To the best of our knowledge, no data on the FDI score are available. Consequently, we derived assumptions from previous studies
[25,26,40-47] that involved the USPHS score
[29], with dimensions close to that of the FDI score
[28]. Thus, we derived assumptions regarding the expected distribution of ratings for the ceramic and composite groups for each of the three dimensions (biological, functional and esthetic). As a proxy for the FDI score, the worst score across the three dimensions, we estimated the three sample sizes required to guarantee a power of 80%, with a type I error rate of 1.7% (Bonferroni adjustment for three dimensions), to detect expected differences in distribution of ratings between the ceramic and composite groups for each dimension. We considered the largest required sample size, which was found for the biological dimension. Consequently, with an overall type I error risk of 5%, a sample size of 211 patients would guarantee 80% power to detect a difference between an expected 3% for scores 3, 4 or 5 in one group and an expected 7% in the other group. Finally, since several centers and several operators will participate, we expected that outcomes from a same center and a same operator will be more similar than those from different centers or different operators. We took this intracenter/operator correlation of data and applied an inflation factor
[48,49], which resulted in an estimated sample size of 358 patients. We will include 400 patients to account for patients lost to follow-up, although we will try to avoid missing data on outcome measures (in particular, by compensating each patient with 100 euros (€100) after 2 years)
[50].

The enrolment capacity was estimated to be 75 patients per year for each hospital and 50 patients per year for each private practice. A 1-year period was planned for including these 400 patients.

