#### Primary outcome analysis

The main analysis will compare the final values of the FDI score (worst score over the three dimensions) between the ceramic and composite groups. The main analysis will be adjusted on the following pre-specified variables: inlay/onlay, premolar/molar, vital/non-vital tooth and operator
[53,55]. An ordinal logistic regression model will be used. The operator variable will be modeled as a random effect. The main analysis will take into account missing outcome data by multiple imputation, with the assumption that data are missing at random. We will report the unadjusted analysis as well; that is, the contingency table showing the distribution of FDI scores in the ceramic and composite groups. The distribution of FDI scores will be compared by Fisher’s exact test. All *P* values will be two-tailed, with significance level 0.05.

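### The unadjusted comparison of the ordered 1–5 FDI score uses Fisher's exact test, which ignores the order and gives no effect estimate; an unadjusted ordinal estimate would be a cheap improvement

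*Protocol article*

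**What the plan says.** All references are to the Protocol article.

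- **Primary outcome.** The endpoint is an ordered score: "The primary outcome is the worst score for all items (ranging from 1 to 5) at 2-year follow-up". A lower score means a better material.
- **Sample size.** The score is handled as ordered: "Since the resulting score is an ordinal variable, we used Zhao’s formula, which is based on the expected distribution of responses". The sizing uses "a power of 80%, with a type I error rate of 1.7% (Bonferroni adjustment for three dimensions").
- **Primary outcome analysis, main analysis.** "An ordinal logistic regression model will be used", adjusted for inlay/onlay, premolar/molar, tooth vitality and operator (a random effect), with multiple imputation of missing outcomes.
- **Primary outcome analysis, unadjusted analysis.** "We will report the unadjusted analysis as well; that is, the contingency table showing the distribution of FDI scores in the ceramic and composite groups". Attached to this table is one test, stated next: "The distribution of FDI scores will be compared by Fisher’s exact test". All p-values are two-sided at 0.05.
- **Secondary outcomes analysis.** The same analyses are carried over to the biological, functional and esthetic dimensions, each at 1.7%. On a plain reading this includes the Fisher comparison.

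**The concern.** One endpoint is treated in two ways. For sizing and for the main model it is ordinal. For the unadjusted comparison its five levels become unordered labels. The trial asks which material has the lower score, and a test blind to order does not address that question.

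Three things are at stake, all in the supporting analysis:

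- With a consistent shift towards better or worse scores, Fisher's test spreads its power over up to four degrees of freedom. It can miss what an ordinal test would detect.
- With a difference that has no net direction, it can give a small p-value that a reader may take to mean one material is better.
- The unadjusted analysis as described has no effect estimate, so a reader has no measure of size or uncertainty to set beside the adjusted odds ratio.

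**Working it through.** **1. Fisher's test ignores order.** With category totals c_k, counts a_k in one arm, n₁ patients in that arm and N in all, the probability of a table with fixed margins is ∏ C(c_k, a_k) / C(N, n₁). The product runs over the categories in any order. Swapping scores 1 and 5, say, leaves every table probability and the p-value unchanged. On a 2 × 5 table no single odds ratio comes with it.

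**2. The article's own figure, 211.** The only distributional input shown is 3% v 7% with scores 3–5 (biological dimension). Two-sided α is 0.017 and power 80%, so z = 2.387 and 0.842, and (2.387 + 0.842)² ≈ 10.42.

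- The two-proportion formula on 3% v 7% gives 618 per arm, 1236 in total. This is not the method the article used, so it does not test 211.
- A formula for ordered categories needs all five shares. I take the tie-corrected rank form for 1:1 allocation (an assumption, since the article does not print the formula): N = (z_α/2 + z_β)² · (1 − Σ m_k³) / [3(θ − ½)²]. Here m_k is the mean share of category k over the two arms, and θ is the probability of a worse score in one arm plus half the probability of a tie.
- Assume score 2 is 10% v 24.7% and scores 3/4/5 split 60/20/20. The arms are then 87/10/1.8/0.6/0.6% and 68.3/24.7/4.2/1.4/1.4%. This gives θ = 0.5933, 1 − Σ m_k³ = 0.5266 and N = 10.42 × 0.5266 / (3 × 0.0933²) ≈ 210, close to 211.
- Score 2 at 5% v 17.7%, or at 20% v 36.9%, also gives about 211.

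So 211 as a total is attainable, but it cannot be confirmed, because the shares of scores 1 and 2 are not given.

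**3. Power of Fisher's test against a tie-corrected Wilcoxon test (simulation).** All category shares below are assumed, apart from the 3% v 7%.

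| Setting | Fisher | Ordinal | Loss (points) |
|---|---|---|---|
| 3% v 7%, total 211, α 0.017 | 71–75% | 82–83% | 6–11 |
| Same, α 0.05 | 83–84% | 91–92% | 7–9 |
| 3% v 7%, 211 per arm, α 0.017 | 61–65% | 79–84% | 16–19 |
| Proportional-odds shift sized for 80% ordinal power, α 0.05, scores spread over 1–5 | 59–61% | about 80% | about 20 |
| Same, most scores 1–2 | 66–70% | 80–82% | 11–14 |

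In the fourth row, Pearson's chi-square stands in for Fisher's test in most runs. Simulation error is about 1 to 2 points, and operator clustering was not simulated. The reading of 211 as a total fits 358 and 400, which are also totals: 358/211 = 1.70, and 1 − 358/400 = 10.5% loss.

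Two other assumed distributions (50/35/9/4/2% and 35/45/12/5/3%), with 179 per arm at α 0.05, give 66–70% v 44–46% at an odds ratio of 1.6. At 1.8 they give 85–86% v 66–67%. That is the top of the range, slightly above 20 points at 1.6.

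**4. Analytic check.** A one-degree-of-freedom test with 80% power at 5% has noncentrality 7.849. The same noncentrality on 2, 3 and 4 degrees of freedom gives 71%, 65% and 60%, so the loss is 9, 15 and 20 points.

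**5. Differences without a consistent direction (assumed shares).**

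- 40/40/12/5/3% v 50/25/12/8/5%: Fisher rejects in 71% of runs, the rank test in 14%.
- 50/27/10/5/8% v 40/42/13/3/2%, 179 per arm: an unordered test (chi-square as stand-in) has about 92% power, the rank test 10%.

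The ranking of the two tests therefore reverses when the shift is not ordered.

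**The case against.** **The test decides nothing.** The main analysis is the adjusted ordinal model. No alpha, sample size or decision rule hangs on the unadjusted table. This stands. A reader might infer that the trial's answer is weakened or clouded, but the article gives the unadjusted result no power to confirm or override the main one.

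**The loss may be modest.** A reader might infer that Fisher's test always has much less power. The article gives category shares only as 3% v 7% for scores 3–5. Calibrated to that and a total of 211, the loss is 6 to 11 points; the losses near 20 need other assumptions. This also stands.

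**An omnibus test has its use.** The Background describes ceramics as more brittle yet more resistant to wear, so a pattern with more of both the best and the worst scores is conceivable. Fisher's test could detect it, whereas an unadjusted proportional-odds model repeats the main model's assumption. This is a reason to keep Fisher's test as a supplement. It is not a reason to make it the only unadjusted comparison of an ordered outcome.

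**An unadjusted odds ratio is not directly comparable with the adjusted one.** Odds ratios are non-collapsible, so the two can differ even with perfect balance. This stands and limits what the fix delivers.

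**A condensed article may leave an effect estimate to the analysis plan.** True of the missing estimate alone. The choice of Fisher's test, however, is stated outright, and it does not match the ordinal treatment of the same score elsewhere in the article.

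A further tempting inference is that 211 is wrong because two proportions of 3% and 7% need 618 per arm. The documents do not support it: the stated method uses the whole distribution, and plausible shares return about 211.

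**Conclusion.** The point holds as a minor one. The stated unadjusted test discards the ordering on which the sizing and the main model rely, and it produces no effect estimate. The same applies to the three dimensions.

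Under an ordered shift the cost is about 6 to 20 percentage points of power. The lower end comes from calibrating to the article's 3% v 7% and a total of 211, and the upper end from scores spread over all five levels. These figures rest on assumed category shares and independent patients. Without an ordered shift, Fisher's test may be the more powerful. The adjusted primary analysis, its odds ratio and the planned sample size are unaffected.

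**What to change.** In Primary outcome analysis, make the unadjusted comparison an unadjusted proportional-odds model reporting the common odds ratio with 95% CI, or a Wilcoxon test with an estimate of the probability of superiority. Run it on the same imputed data sets as the main analysis. Keep the contingency table as description. If Fisher's test is retained, label it a supplementary omnibus check that carries no direction. The same wording then serves the three dimensions.

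The cost is one or two sentences and no extra data. The downside is that the unadjusted odds ratio rests on proportional odds. State also that it may differ from the adjusted odds ratio through non-collapsibility, so that such a difference is not read as confounding.

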#### Secondary outcomes analysis

The same analyses will be used to compare both treatments by each of the three dimensions (with an α risk of 1.7% for each dimension). Secondary analyses will also involve FDI items, quantified analysis of wear (by silicone impressions) and analysis of the overall quality of the restoration (assessed by dentists).

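### Holm's step-down test would serve the three FDI dimension tests at least as well as a fixed 1.7% Bonferroni level, at the same 5% familywise error; the gain depends on how many dimensions differ

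*Protocol article*

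**What the plan says.** The Secondary outcomes analysis section of the protocol article repeats the primary model to "compare both treatments by each of the three dimensions (with an α risk of 1.7% for each dimension"). It mentions no step-down or other sequential procedure.

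The Sample size section shows where the level comes from. It sizes the trial "with a type I error rate of 1.7% (Bonferroni adjustment for three dimensions"), and then describes the result as obtained "with an overall type I error risk of 5"%. On power it says "we estimated the three sample sizes required to guarantee a power of 80"%, in order "to detect expected differences in distribution of ratings between the ceramic and composite groups for each dimension". It then says: "We considered the largest required sample size, which was found for the biological dimension".

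The primary test is separate. It compares the worst score between arms, and the Primary outcome analysis section states that P "values will be two-tailed, with significance level 0.05".

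**The concern.** A single-step Bonferroni rule holds every dimension to 1.7% whatever the other two show. Once one dimension has been rejected at 5%/3, only two hypotheses remain, and the 5% familywise limit allows the next to be tested at 2.5% and the last at 5%. Holm's procedure uses that room and the fixed level does not.

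The dimension tests matter for interpretation. The primary outcome is a worst score, so it cannot show whether a difference is biological, functional or esthetic. The biological dimension needed the largest sample, so it has the least power to spare. What is at stake is power in these secondary comparisons. The validity of the trial and its primary test are not affected.

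**Working it through.** **The plan's level.** 0.05 / 3 = 0.01667, printed as 1.7%. This is reproduced.

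**The plan's 80%.** It is taken as the design value. The section gives the size as "a sample size of 211 patients would guarantee 80% power to detect a difference between an expected 3% for scores 3, 4 or 5"; the rate assumed for the opposite arm is 7%. The split between scores 1 and 2 is not printed, so 211 can be neither confirmed nor refuted from the article.

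**Setup.** Three two-sided normal test statistics; a real effect has 80% power at 0.05/3.
- Noncentrality: 2.394 + 0.842 = 3.236.
- Power of that effect at 2.5%: Φ(3.236 − 2.241) = 84.0%.
- Power at 5%: Φ(3.236 − 1.960) = 89.9%.
- Holm compares the smallest p-value with 0.05/3, the next with 0.05/2 and the largest with 0.05, and stops at the first failure.

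A real effect therefore falls below 0.05/3 with probability 0.800, between 0.05/3 and 0.025 with probability 0.840 − 0.800 = 0.040, and between 0.025 and 0.05 with probability 0.899 − 0.840 = 0.059. For a null dimension the same bands have probabilities 0.0167, 0.0083 and 0.025.

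**Independent statistics, by hand.** Under Holm a dimension is rejected in three cases: it is below 0.05/3; it is in the middle band and at least one other is below 0.05/3; or it is in the upper band, both others are below 0.025, and at least one of them is below 0.05/3.

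- *All three differ.* 0.800 + 0.040 × (1 − 0.2²) + 0.059 × (0.840² − 0.040²) = 0.800 + 0.038 + 0.042 = **88.0%**, against 80%.
- *Two differ.* 0.800 + 0.040 × (1 − 0.2 × 0.9833) + 0.059 × (0.840 × 0.025 − 0.040 × 0.0083) = 0.800 + 0.032 + 0.001 = **83.3%**.
- *One differs.* 0.800 + 0.040 × (1 − 0.9833²) + a negligible term = **80.1%**.
- *False positive on a null dimension when the other two differ.* 0.0167 + 0.0083 × 0.96 + 0.025 × 0.704 = **4.2%**, against 1.7% under Bonferroni.

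**Correlated statistics.** The documents give no correlation between dimensions, so a range is assumed. Simulated Holm power per dimension (equal correlations), starting from 80% under Bonferroni:

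| Correlation | All three differ | Two differ |
|---|---|---|
| 0 | 88.0% | 83.3% |
| 0.3 | 87.1% | 83.0% |
| 0.5 | 86.4% | 82.8% |
| 0.6 | 86.1% | not run |
| 0.8 | 85.2% | 82.3% |
| 0.9 | 84.5% | not run |

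With one real effect, power stays at 80.0-80.2% at correlations of 0, 0.3, 0.5 and 0.8.

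**Unequal starting power.** The biological dimension set the sample size, so the other two start at 80% or more. If they are at 90% (assumed), Holm takes the biological dimension from 80% to 89.0%, 88.4%, 88.1% and 87.8% at correlations 0, 0.3, 0.5 and 0.8. The other two reach about 93-95%.

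**Error control.** With no real effect, Holm and Bonferroni have identical familywise error: 4.9% at correlation 0 and 3.5% at 0.8. With one or two real effects, Holm's stays at or below 4.6%.

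**The case against.** Nothing here is wrong or contradictory. The trial is sized and analysed at the same 1.7%, familywise error is controlled, and only secondary tests are involved. All of that stands.

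A reader might infer that Holm lifts every dimension from 80% to 86-88% as a matter of course. The documents do not support that. The figure needs a true difference in all three dimensions, each at exactly 80% power, with correlation no higher than about 0.6. The Sample size section does plan for a difference in each dimension. However, the Background reports no clear evidence of a difference in either earlier randomized study, and the Research in context section says that one of them favoured composite on only two items. One or two real effects are therefore plausible, and the gain is then 0 to 3 points. Nor do all three dimensions start from 80%: only the biological one is pinned there.

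Bonferroni is also stricter when some dimensions are null. With two real effects and independence, the third is falsely declared different 1.7% of the time under Bonferroni and 4.2% under Holm. With one real effect, familywise error is 3.3% (1 − 0.9833²) against 4.6%. This matters for tests meant to locate a difference, but both stay inside the 5% that the plan chose.

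Finally, a fixed level pairs directly with 98.3% confidence intervals and Holm has no equally simple counterpart. The article describes no such intervals for the dimensions, but it is condensed and the full protocol is not shown, so this remains a real if small cost.

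**Conclusion.** The point holds as an efficiency improvement. Compared with Bonferroni at 5%/3, Holm keeps the same 5% familywise limit under any dependence and rejects at least as much in every scenario.

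Per-dimension power rises from 80% to about 86-88% if all three dimensions differ as planned (correlation 0 to 0.6; about 85% at 0.8), to about 82-83% if two differ, and hardly at all if one differs. The biological dimension gains 8-9 points if the other two have 90% power. These figures rest on the plan's unverified 80%, on normal test statistics, and on assumed correlations. The 5% in question covers the family of three dimensions only; the primary test has its own 5%.

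A reader might also infer from 3 × 1.7% = 5.1% that the plan overspends its error rate. It does not: the Sample size section names a Bonferroni adjustment for three dimensions within an overall 5%, so 1.7% is simply 0.05/3 rounded.

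**What to change.** In the Secondary outcomes analysis section, replace the bracketed fixed level by: *using Holm's step-down procedure across the three dimensions at a familywise two-sided 5% (0.05/3, 0.05/2, 0.05)*, and report Holm-adjusted p-values. Make the change before the outcome data are analysed.

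The cost is one sentence. The design, data collection, primary analysis and sample size are untouched, and the 1.7% used for sizing can stay because it is the first Holm step. If intervals for the dimensions are wanted, state their level separately and note that they do not correspond exactly to the Holm decisions.

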#### Subgroup analyses

We will perform subgroup analyses
[56] of the following variables: inlay/onlay, premolar/molar, vital/non-vital tooth, inlay/onlay volume, canine or group lateral guidance and occlusal tapping before luting of the inlay/onlay. If interaction tests are performed for six subgroups independent of each other and each at a significance level of 5% (two-sided), the risk of finding at least one false-positive statistically significant interaction (that is, due to sampling fluctuations) is 26% (= 1 − (1 – 0.05)^6^).

## Discussion

For clinicians, the CECOIA trial will help provide evidence-based recommendations concerning the choice of material for inlay/onlay restorations. However, because the manufacturing technique explains part of the inlay/onlay’s properties, the results concerning ceramic and composite inlay/onlay manufacturing will be applicable only for CAD/CAM inlays/onlays and not for traditionally manufactured inlays/onlays. In particular, CAD/CAM composite blocks contain few monomers, which could limit biological failures as compared with traditionally manufactured composites; ceramic blocks present better mechanical properties initially but milling may induce fissures. However, the materials still have a similar composition and this trial may give an idea of their clinical performance.

For patients who receive CAD/CAM inlays/onlays, this trial may lead to an improvement in the longevity of the restorations. For researchers, it may provide ideas for further research concerning the efficacy and prognosis of inlays and onlays.

## Trial status

The trial was submitted for registration at ClinicalTrials.gov on 10 September 2012. Patient recruitment started on 14 September 2012. This protocol was submitted for publication on 20 November 2012. General information about the trial (such as the original protocol submitted to the ethics committee) can be obtained on the trial’s website (http://cecoia.fr). We will share the data obtained.

## Abbreviations

ANSM: Agence Nationale de Sécurité du Médicament et des Produits de Santé; AP-HP: Assistance Publique – Hôpitaux de Paris; CAD/CAM: Computer-assisted design/computer-assisted manufacturing; CECOIA: CEramic and COmposite Inlays Assessment; CONSORT: Consolidated Standards of Reporting Trials; CPP: Comité de Protection des Personnes; CRF: Case report form; DRCD: Département de la Recherche Clinique et du Développement; FDI: Fédération Dentaire Internationale; HEGP: Hôpital Européen Georges-Pompidou; ICH: International Conference on Harmonisation; PHRC: Programme Hospitalier de Recherche Clinique; RCT: Randomized controlled trial; USPHS: US Public Health Service; SPIRIT: Standard Protocol Items: Recommendations for Interventional Trials; WHO: World Health Organization.
